## Abstract

**Introduction::**

In patients with malignant distal bile duct obstruction and normal gastrointestinal anatomy, endoscopic ultrasound-guided choledochoduodenostomy (EUS-CDS) is indicated when endoscopic retrograde cholangiopancreatography (ERCP) fails. The ERCP drainage route passes through the tumor, whereas the EUS-CDS route does not. Therefore, EUS-CDS is expected to have a longer stent patency than ERCP. However, for first-line biliary drainage, it remains unclear whether EUS-CDS or ERCP is superior in terms of stent patency. To reduce the frequency of highly adverse events (AEs) such as bile peritonitis or stent migration following EUS-CDS, we developed an antimigration metal stent with a thin delivery system for tract dilatation. This study is designed to assess whether EUS-CDS with this novel stent is superior to ERCP with a traditional metal stent in terms of stent patency when the two techniques are used for first-line drainage of malignant distal biliary obstruction.

**Methods/design::**

This study is a multicenter single-blinded randomized controlled trial (RCT) involving 95 patients in four tertiary centers. Patients with malignant distal biliary obstruction that is unresectable or presents a very high surgical risk and who pass the inclusion and exclusion criteria will be randomized to EUS-CDS or ERCP in a 1:1 proportion. The primary endpoint is the stent patency rate 180 days after stent insertion. Secondary outcomes include the rates of technical success, clinical success, technical success in cases not requiring fistulous-tract dilation (only EUS-CDS group), procedure-related AEs, re-intervention success, patients receiving post-drainage chemotherapy, procedure time, and overall survival time.

**Discussion::**

If EUS-CDS is superior to ERCP in terms of stent patency and safety for the first-line drainage of malignant distal biliary obstruction, it is expected that the first-line drainage method will be changed from ERCP to EUS-CDS, and that interruption of chemotherapy due to stent dysfunction can be avoided.

**Trial registration::**

University Hospital Medical Information Network Clinical Trials Registry (UMIN-CTR), ID: UMIN000041343. Registered on August 6, 2020. https://upload.umin.ac.jp/cgi-open-bin/ctr_e/ctr_view.cgi?recptno=R000047201

Version number: 1.2, December 7, 2020.

## Introducion

1

The criterion standard procedure for malignant biliary drainage is transpapillary drainage with endoscopic retrograde cholangiopancreatography (ERCP).^[1,2]^ However, in 20% to 40% of patients, the insertion of a metal stent through the tumor leads to subsequent stent dysfunction secondary to tumor tissue stent ingrowth and/or overgrowth,^[3,4]^ and EUS-guided biliary drainage (EUS-BD) has recently become the modality of choice when ERCP fails.^[5]^ One such EUS-BD method, which was first described in 2001,^[6]^ is EUS-guided choledochoduodenostomy (EUS-CDS), where an anastomosis is created between the duodenal bulb and the extrahepatic bile duct. Patients with distal biliary obstruction and normal gastrointestinal anatomy may be candidates for EUS-CDS, which is not subject to tumor tissue ingrowth or overgrowth of the stent, unlike transpapillary drainage with ERCP.

Some studies have reported comparisons of EUS-BD and ERCP in first-line biliary drainage. Paik et al^[7]^ reported an randomized controlled trial (RCT) that found EUS-BD to have a higher stent patency rate than ERCP (85% vs 49%, respectively), but 2 other RCTs reported that EUS-BD had comparable stent patency to ERCP^[8,9]^; the differences in stent patency between EUS-BD and ERCP therefore remains unclear.

We previously developed a metal stent suitable for EUS-CDS (Covered BileRush Advance, Piolax Medical Devices, Yokohama, Japan; Figure 1)^[10]^ and reported a prospective multicenter study that showed EUS-CDS with this metal stent to have 95% technical and 100% clinical success rates, with procedure-related adverse events (AEs) reported in 5% of cases.^[11]^ Therefore, this study is designed to assess whether EUS-CDS with the novel stent offers superior stent patency to ERCP with a traditional metal stent when used as a first-line drainage method for malignant distal biliary obstruction.

**Figure 1 F1:**
[figure not shown]
The stent and delivery system (Covered BileRush Advance, Piolax Medical Devices, Yokohama, Japan). (A) The expanded stent has a diameter of 8 mm and is 60 mm in length. It is made of laser-cut nitinol wire and is partially covered by a silicone membrane. A 5-mm section at the proximal end of the stent is uncovered and flared to a diameter of 10.5 mm to prevent distal migration. The distal end is also flared to a diameter of 10.5 mm to prevent inward migration. (B) This stent is delivered with a 7.0-Fr pull-back delivery catheter. The tip of the delivery system is shaped (2.6 Fr) to enable stent deployment without fistula dilation.

## Methods/design

2

### Ethics approval and patient consent

2.1

This study is approved by the Wakayama Medical University Ethics Committee (No. 2958), and informed consent will be obtained from all patients. The trial is registered with the University Hospital Medical Information Network (trial registration no. UMIN000041343). This protocol was prepared in conformance with the Standard Protocol Items: Recommendations for Interventional Trials (SPIRIT) guidelines [see Additional file 1].

### Study aims and design

2.2

This study is a multicenter prospective RCT across four tertiary centers in Japan, comparing first-line biliary drainage for malignant distal bile duct obstruction between EUS-CDS and ERCP (Fig. 1). We hypothesize that EUS-CDS with the novel stent is superior in terms of stent patency to ERCP with a traditional metal stent when the procedures are used as first-line drainage for malignant distal biliary obstruction. We expect that EUS-CD with the novel stent will allow avoidance of interruption to chemotherapy due to stent dysfunction, and will thereby ultimately improve survival time.

### Patients

2.3

At each center, the on-site study investigators will obtain informed consent from the candidates, and they will use an electronic data capture system to input necessary information, confirm that the candidates meet the eligibility criteria (ie, the candidates meet all the inclusion criteria and none of the exclusion criteria), and register the candidates with the registration secretariat. After confirming that a candidate meets the criteria, a registration number will be issued, and the registration will be considered complete. Patients who have completed the registration will be randomly assigned (1:1) to receive EUS-CDS or ERCP for relief of biliary obstruction. A flowchart of the study design is shown in Figure 2.

**Figure 2 F2:**
[figure not shown]
Flowchart of the study design.

### Inclusion criteria

2.4

The following inclusion criteria will be applied:

1.Age ≥ 20 years.2.Radiological diagnosis (with or without pathological confirmation) of malignancy and presence of a malignant distal biliary obstruction and dilation of the upstream bile duct that is unresectable or presents a very high surgical risk.3.Written consent obtained following adequate explanation of the study aims, design, and procedures.

### Exclusion criteria

2.5

The following exclusion criteria will be applied:

1.Radiological evidence of gastric outlet obstruction on CT.2.Hilar biliary obstruction.3.Surgically altered anatomy.4.ECOG performance status of 4.5.Poorly controlled ascites.6.History of endoscopic sphincterotomy (EST).7.Biliary stenting.8.Serious complication involving another organ.9.Uncorrectable coagulopathy and/or thrombocytopenia.10.Any other condition or situation determined by a study investigator to represent a reason for ineligibility.

### Randomization and blinding

2.6

Subjects will be assigned to one of the treatment methods at a ratio of 1:1 by dynamic allocation according to a web-based registration program system. Based on the baseline factors for treatment allocation, including primary disease (pancreatic cancer or not) and institution is computed. The registration secretariat will strictly control the program to prevent leakage of the assignment information to other involved personnel. Blinding will not be used in this study.

### EUS-CDS procedure

2.7

An echoendoscope is inserted orally and advanced to the duodenal bulb. Biliary accessibility is then confirmed via EUS from the duodenal bulb, with Doppler imaging used to rule out any intervening vessels. A 19-gauge fine aspiration needle is used to puncture the extrahepatic bile duct under endosonographic guidance. After the bile juice is aspirated, contrast medium is injected and a 0.025 inch guidewire is advanced into the common bile duct. Thereafter, an attempt is made to insert the novel stent (8 mm; Covered BileRush Advance, Piolax Medical Devices, Yokohama, Japan) via the fistula without using any dilation devices. If successful, the metal stent is expanded between the common bile duct and the duodenum under EUS guidance. If the delivery system cannot be advanced via the fistula, the fistulous tract is dilated using dilation devices. The stent diameter is 8 mm, and the stent length is determined at the discretion of the endoscopist.

### ERCP procedure

2.8

ERCP-assisted transpapillary stenting is performed using a standard duodenoscope. Following biliary cannulation, contrast medium is injected to obtain a cholangiogram.

After confirmation of successful bile duct cannulation, biliary sphincterotomy is performed. Finally, a fully covered self-expandable metal stent (X-Suit NIR; Olympus Medical Systems, Tokyo, Japan) is placed across the papilla and the biliary stricture. The stent diameter is 10 mm, and the stent length is determined at the discretion of the endoscopist.

### Primary endpoint

2.9

The primary endpoint is the stent patency rate at 180 days after stent insertion. The stent patency rate is defined as the percentage of patients who do not experience stent dysfunction from the date of stent insertion to 180 days after treatment.

Stent dysfunction is defined as follows:

1.If the lowest serum total bilirubin (T-Bil) value in the blood tests performed after treatment is <1.5 mg/dL: a serum T-Bil level of ≥3.0 mg/dL and a bile duct diameter greater than that on the pretreatment imaging.2.If the lowest serum T-Bil value in the blood tests performed after treatment is more than 1.5 mg/dL: a serum T-Bil level >2.0 times the lowest value and a bile duct diameter greater than that on the pretreatment imaging.

Patients who are lost to follow-up or who die without stent dysfunction will be censored at the last observation date. Patients without technical success will be censored at the treatment date.

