### Secondary endpoints

2.10

The secondary endpoints are as follows:

1.Technical success rate: Technical success is defined as the stent being placed between the duodenum and common bile duct at 1 day after treatment in the EUS-CDS group, and the stent being placed across the papilla and the biliary stricture on CT at 1 day after treatment in the ERCP group.2.Clinical success rate: Clinical success is defined as improvement in T-Bil to less than 1.3 mg/dL or improvement in T-Bil or alkaline phosphatase levels to <50% of the highest pretreatment values within 14 days after treatment.3.Procedure-related AE rate: Early AEs (within 14 days after treatment) are defined according to the Cotton criteria^[12]^ and the ASGE lexicon for endoscopic AEs,^[13]^ and include postprocedural pancreatitis, cholecystitis, non-occlusion cholangitis, stent migration, stent deviation, liver abscess, bleeding, intestinal perforation, and abdominal pain. Late AEs (>14 days until 180 days after treatment) are defined according to the ASGE lexicon for endoscopic AEs, and include nonocclusion cholangitis, stent migration, and stent deviation.4.Procedure time: Procedure time is defined as the time from the puncture of the bile duct to stent placement in the EUS-CDS group, and from the time of biliary cannulation to stent placement in the ERCP group.5.Re-intervention success rate: Re-intervention success is defined as the placement of a new drainage tube at the fistula in the EUS-CDS group, and the placement of a new transpapillary drainage tube in the ERCP group.6.Technical success rate in cases not requiring fistulous-tract dilation (only EUS-CDS group).7.Overall survival time.8.Rate of patients receiving post-drainage chemotherapy: The rate of post-drainage chemotherapy is defined as the percentage of patients who receive at least 2 courses of chemotherapy after drainage.

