### Data collection

2.11

Baseline assessment will be performed during the screening period. Basic information including sex, age, date of birth, date of obtaining informed consent, history of EST, presence of biliary stenting, and assessment of performance status will be recorded retrospectively. To ensure feasibility and safety, complete blood counts, hepatic and renal function tests, and biochemical tests will be performed during the screening period.

Computed tomography (CT) will be performed during the screening period to diagnose the tumor stage according to the TNM classification, to determine the site of biliary obstruction, and to determine the presence of gastric outlet obstruction. Patients will undergo the above-mentioned blood tests on post-procedure days 1, 3, 14, 30, 90, and 180 to evaluate the efficiency of the treatment, AEs, and stent dysfunction. CT will be performed postoperatively on days 1, 14, and 180 to evaluate the position of the stent, AEs, and stent dysfunction. The schedule for enrollment, interventions, and assessments is shown in Figure 3.

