### Follow-up

2.12

All patients will be followed until either death or 180 days after the treatment of the last registered patient. If the patient is unable to attend hospital, follow-up will be conducted over the phone. If follow-up information cannot be obtained, the patient will be considered lost to follow-up, and their data will be documented accordingly.

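### Stent dysfunction counts only if the duct becomes wider than its obstructed pretreatment width, so a re-occluded and replaced stent can be scored as patent

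*Protocol article*

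**What the plan says.** Section 2.9 makes the primary endpoint the proportion of patients free of stent dysfunction to 180 days. Dysfunction has two rules, chosen by the lowest total bilirubin (T-Bil) after treatment:

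- Lowest value below 1.5 mg/dL: "a serum T-Bil level of ≥3.0 mg/dL and a bile duct diameter greater than that on the pretreatment imaging".
- Lowest value above 1.5 mg/dL: "a serum T-Bil level >2.0 times the lowest value and a bile duct diameter greater than that on the pretreatment imaging".

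In both rules the bilirubin limb must be met together with the diameter limb, "a bile duct diameter greater than that on the pretreatment imaging". Section 2.4, criterion 2, admits only patients with "presence of a malignant distal biliary obstruction and dilation of the upstream bile duct".

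The censoring rules in section 2.9 cover loss to follow-up, death without dysfunction, and technical failure (censored on the treatment date). They do not mention re-intervention or stent exchange. Section 2.10 uses re-intervention only for a secondary success rate. It lists late adverse events that "include nonocclusion cholangitis, stent migration, and stent deviation", so migration is not in itself dysfunction. Section 2.11 schedules imaging as follows: "CT will be performed postoperatively on days 1, 14, and 180".

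**The concern.** The diameter limb should detect a duct that drained and then became blocked again. The natural reference is the duct after successful drainage. The plan instead uses the duct at its obstructed width, so part of the re-dilation caused by a blocked stent is defined away.

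The missing rule for re-intervention makes this worse. In practice a blocked stent is likely to be dealt with before the duct exceeds its original dilated width. Under the text as written, that patient has no event and continues to contribute patent time with a different stent. The Discussion values longer patency because it would reduce re-interventions and avoid chemotherapy delay. An endpoint that can miss the failures leading to re-intervention does not measure that benefit well.

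At stake are the meaning of the reported patency rates and the number of events available to the log-rank test.

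**Working it through.** **1. Reading the definition.** Let D0 be the duct diameter on pretreatment imaging and D1 the smaller diameter after drainage. A re-occlusion that brings the duct to any width between D1 and D0 fails the diameter limb, so it is not an event under either rule, whatever the bilirubin. Pretreatment cannot sensibly mean before a re-intervention: section 2.10 uses the same word, in the clinical success definition, for values before the drainage procedure.

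**2. Gap at 1.5 mg/dL.** Rule 1 needs a lowest value below 1.5 and rule 2 one above 1.5. A lowest value of exactly 1.5 meets neither.

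**3. Lowest value without a time limit.** For a lowest value L above 1.5, rule 2 needs T-Bil above 2 × L, which is more than 3.0 mg/dL. If a later re-drainage takes T-Bil below 1.5, rule 1 applies to the whole course and the threshold drops to 3.0. A peak of at least 3.0 but not above 2 × L then meets the bilirubin limb or not, depending on blood tests taken after the episode.

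**4. The plan's own design figures (section 3.1).** Inputs: 180-day patency 85.1% and 48.9%, exponential times, two-sided alpha 0.01, power 90%, 12 months' enrolment, 6 months' further observation, 10% deaths per month.

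- Hazard ratio = ln(0.851) / ln(0.489) = 0.2255.
- Schoenfeld events = 4 × (z for 0.995 + z for 0.90)² / (ln 0.2255)² = 26.8, so 27; the plan states 29.
- Mean event probability over 6 to 18 months' follow-up, with death as a competing exponential: (0.492 + 0.161) / 2 = 0.327 with a monthly death hazard of 0.10, or 0.320 with −ln(0.9). Then 29 / 0.327 = 88.8 and 29 / 0.320 = 90.6; the plan states 90.
- 90 / 0.95 = 94.7, so 95, as stated.

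The planned size therefore assumes that every dysfunction is counted.

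**5. Effect of missed dysfunctions.** The captured share is not in the documents; 50% to 100% is assumed, equal in both arms. Simulation: 90 patients, the hazards above, 10% deaths per month, follow-up 6 to 18 months, two-sided log-rank test at 0.01. There are two versions. In A, a patient whose dysfunction is missed never has a later event. In B, a later event can still be captured (hazard multiplied by the captured share).

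| Captured share | Events, A | Power, A | Events, B | Power, B |
|---|---|---|---|---|
| 100% | 29 | 0.88 | 29 | 0.89 |
| 90% | 26 | 0.81 | 27 | 0.86 |
| 75% | 22 | 0.64 | 24 | 0.79 |
| 50% | 14–15 | 0.35 | 18 | 0.60 |

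Repeat runs, with either conversion of the death rate, agree to within about 0.02. The Schoenfeld formula is milder under B, at 0.70 to 0.71 for 50% capture; it is an approximation, and the effect here is large and the events few.

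**6. Effect on the reported rates.** Under B with 70% capture, apparent patency would be 0.489^0.7 = 60.6% and 0.851^0.7 = 89.3%. The difference is 28.7 points instead of 85.1 − 48.9 = 36.2.

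**The case against.** The strongest defence is that blinding is not used (section 2.6), so a rule built on laboratory values and imaging protects the endpoint from the operator's judgement, whereas re-intervention is partly that operator's decision. This stands as a reason to keep the present rule as a sensitivity analysis. It does not justify an obstructed duct as the comparator, since post-drainage imaging is just as objective.

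It is also fair that the captured share is unknown and that version A is a harsh assumption. The power figures are a range under stated assumptions, not a prediction.

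Several stronger readings are tempting but unsupported:

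- *The endpoint favours EUS-CDS because migration is left out.* Migration is an adverse event in both arms, the ERCP stent is a fully covered metal stent (section 2.8), and a migration that meets both limbs still counts. About 22 of the 29 expected events fall in the ERCP arm, so equal under-capture would lose mostly ERCP events. The direction is unknown.
- *Reported EUS-CDS patency would be inflated by a known amount.* The 17.9% to 23.3% adverse event range in the Discussion comes from earlier EUS-CDS experience, and the share needing re-drainage for migration is not given. For this stent the article reports 5% procedure-related adverse events of all kinds.
- *Stents that never drain are scored as patent, as a separate error.* Section 2.10 measures initial drainage as clinical success, and technical failures are censored. Separating initial failure from later loss of patency is a design choice.
- *Telephone follow-up, or the lack of scheduled CT between days 14 and 180, is an error of its own.* Nothing says a call sets the patency censoring date, and a schedule does not exclude imaging on suspicion.
- *A patient at exactly 1.5 mg/dL can never have an event.* A later, lower value would bring rule 1 into play.

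**Conclusion.** The point holds on the text alone. The diameter limb is compulsory in both rules and compares with a duct that had to be dilated at entry. No event or censoring rule covers re-intervention, so following the plan exactly can classify a re-occluded and replaced stent as patent. The gap at 1.5 mg/dL and the open-ended lowest value are smaller wording faults in the same definition.

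The size depends on a captured share that the documents do not give. At 90% capture the loss of power is modest (to 0.81–0.86). At 75% and below it is material (0.64–0.79, then 0.35–0.60). These figures assume equal capture in the two arms and the planned hazards. With unequal capture the comparison would be biased, in a direction that cannot be determined from the documents.

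**What to change.** Amend section 2.9 before any comparison by arm:

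1. Compare duct diameter with post-drainage imaging: the day-14 CT, or the day-1 CT for failures before day 14.
2. Count re-intervention for biliary obstruction or loss of stent function, including migration that needs re-drainage, as dysfunction on its date.
3. Use the lowest T-Bil up to the date being assessed.
4. Change rule 2 to apply at ≥1.5 mg/dL. At 1.5 its threshold is above 3.0 mg/dL, which joins on to rule 1.
5. Keep the present definition as a sensitivity analysis.

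The cost is small. The day-1 and day-14 CTs and the T-Bil tests are already scheduled (section 2.11), and re-intervention already feeds a secondary endpoint. The indication for each re-intervention must be recorded, which the article does not show. The drawback is that re-intervention is partly a clinician's decision in an unblinded trial; the sensitivity analysis on the present rule shows how far the result depends on it.

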### Sample size calculation

3.1

In this study, we assume that the stent patency rate at 180 days after stent insertion will be 85.1% in the EUS-CDS group and 48.9% in the ERCP group.^[9]^ In this case, assuming an exponential distribution for the survival time distribution, when the null hypothesis “stent patency rates at 180 days after stent insertion in the EUS-BD and ERCP groups are the same” is tested against the 2-sided alternative hypothesis “stent patency rates at 180 days after stent insertion in the EUS-BD and ERCP groups are different,” using a two-sample log-rank test at a significance level of α = 0.01 (2-sided), the number of events required to achieve a power of 1-βof 90% is 29. If the enrollment period is 12 months, the observation period after the last case enrollment is 6 months, and the death rate per month is 10.0% in both groups, then the minimum number of cases required is 90. Therefore, we have set a target number of 95 cases, assuming 5% are ineligible.

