### Statistical analysis

3.2

In the effectiveness analysis for the population, analysis of the full analysis set is the main analysis, and per protocol analysis is performed as a reference. The safety analysis for the target population will analyze all test examples. For the stent patency rate at 180 days after stent insertion, the *P* value for the difference between the two procedures will be calculated using a 2-sample log-rank test. The Kaplan–Meier method will be used to estimate survival curves for each group. Greenwood's formula will be used to estimate the confidence interval for the stent patency rate at 180 days after stent insertion, and Brookmeyer and Crowley's method will be used to estimate the confidence interval for the median rate. For the rates of technical success, clinical success, technical success in cases not requiring fistulous-tract dilation, procedure-related AEs, re-intervention success, and patients receiving post-drainage chemotherapy, the percentages, and 99% confidence intervals will be calculated for each group. For the procedure time, the mean and 99% confidence interval will be calculated for each group. For the overall survival time, the *P* value for the difference between the 2 groups will be calculated with a 2-sample log-rank test. A *P* value of ≤.01 will be considered statistically significant. All analyses will be performed using JMP Pro version 14 (SAS Institute, Inc., Cary, NC).

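### The 180-day patency rate is defined as a percentage of patients, but Kaplan-Meier with deaths censored estimates a different quantity: patency had patients not died

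*Protocol article*

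**What the plan says.** All of this is in the protocol article.

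- **Definition (2.9, Primary endpoint).** The wording for the 180-day endpoint: "defined as the percentage of patients who do not experience stent dysfunction from the date of stent insertion to 180 days after treatment".
- **Deaths (2.9).** "Patients who are lost to follow-up or who die without stent dysfunction will be censored at the last observation date". Patients without technical success are censored on the day of treatment.
- **Estimation (3.2, Statistical analysis).** For the curves, the Kaplan-Meier "method will be used to estimate survival curves for each group". The arms are compared by a two-sample log-rank test. For the interval, "Greenwood's formula will be used to estimate the confidence interval for the stent patency rate at 180 days after stent insertion". No scale and no confidence level are given for that interval. For the secondary rates, "the percentages, and 99% confidence intervals will be calculated for each group".
- **Expected mortality (3.1, Sample size calculation).** "the death rate per month is 10.0% in both groups", alongside assumed 180-day patency of 85.1% (EUS-CDS) and 48.9% (ERCP) with exponential times.

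Death is not treated as a competing event anywhere in the document.

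**The concern.** A patient who dies on day 60 with a working stent has not experienced dysfunction. Under the definition, that patient counts among the successes. Under the censoring rule, the patient leaves the risk set on day 60, and Kaplan-Meier in effect assumes the same later risk of dysfunction as in patients still alive. The definition and the estimator therefore answer different questions. The first asks what share of patients have dysfunction by day 180. The second asks what share would have it if death did not intervene.

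With few deaths the two nearly coincide. In this population the protocol expects close to half of the patients to die within the window.

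The distinction matters for interpretation. The Discussion and Conclusions tie better patency to fewer re-interventions and fewer interruptions of chemotherapy. Those are events in actual patients, some of whom die first. If Kaplan-Meier rates are read as shares of patients, dysfunction is overstated, and more so in the ERCP arm.

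**Working it through.** **Inputs, all from section 3.1:** 180-day patency S = 0.851 (EUS-CDS) and 0.489 (ERCP); exponential times; 10.0% deaths per month in both arms; two-sided alpha 0.01; power 90%; 12 months of enrolment and 6 months of further follow-up; 29 events; 90 patients. I take 6 months as 180 days. I also assume that dysfunction and death are independent, which the article does not state but which ordinary censoring implies, and no other loss to follow-up.

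**Step 1: the plan's own figures.**
- Hazard ratio = ln 0.851 / ln 0.489 = 0.2255.
- Schoenfeld events = 4(2.576 + 1.282)² / (ln 0.2255)² = 26.8, so 27. The stated 29 is within two of this and gives 92.4% power.
- The probability of an event per patient is λ/(λ+μ) × [1 − (e^(−6(λ+μ)) − e^(−18(λ+μ))) / (12(λ+μ))], averaged over the arms. With μ = −ln 0.9 it is 0.320, and 29 / 0.320 is about 90.6. With μ = 0.10 it is 0.327, and N is about 88.8. The stated 90 lies between them.
- 90 / 0.95 = 94.7, so 95.

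The calculation therefore treats 85.1% and 48.9% as patency net of death, and it already allows for deaths.

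**Step 2: monthly hazards.**
- Dysfunction: λ = −ln(S)/6 = 0.0269 (EUS-CDS) and 0.1192 (ERCP).
- Death: μ = −ln 0.9 = 0.1054.
- Deaths by 6 months: 1 − 0.9⁶ = 46.9%.

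**Step 3: the two quantities at 6 months.**
- Kaplan-Meier target: 1 − e^(−6λ).
- Share of patients with dysfunction, death competing: λ/(λ+μ) × (1 − e^(−6(λ+μ))).
- EUS-CDS: 0.0269/0.1323 × (1 − 0.4523) = 0.111.
- ERCP: 0.1192/0.2246 × (1 − 0.2599) = 0.393.

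| At 6 months | EUS-CDS | ERCP |
|---|---|---|
| Dysfunction, Kaplan-Meier target | 14.9% | 51.1% |
| Dysfunction, share of patients | 11.1% | 39.3% |
| Excess of the first over the second | 3.8 points | 11.8 points |
| Death before any dysfunction | 43.6% | 34.7% |
| Alive with a patent stent | 45.2% | 26.0% |
| Patency as defined in 2.9 | 88.9% | 60.7% |

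In 45 patients per arm, the share as defined corresponds to 45 × 0.111 = 5.0 and 45 × 0.393 = 17.7 patients with dysfunction. Reading the Kaplan-Meier value as a share would suggest 45 × 0.149 = 6.7 and 45 × 0.511 = 23.0.

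**Step 4: sensitivity.** If 10% is read as a hazard (μ = 0.10), 45.1% die by 6 months and the shares are 11.3% and 39.8%. The gap between the arms is 36.2 points on the Kaplan-Meier scale whatever the mortality. As shares of patients it is 28.2 points at 10% monthly mortality, 31.9 at 5% and 24.9 at 15%.

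**Step 5: the interval.** In simulations of 20,000 arms with 45 patients and μ = 0.1054, untransformed 99% Greenwood limits covered 95.0% (EUS-CDS) and 98.2% (ERCP). In EUS-CDS the upper limit exceeded 100% in 62% of runs. Log(-log) limits from the same variance covered 99.0% and 99.2%. Runs without any event (under 0.5%, EUS-CDS only) were left out.

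**The case against.** The strongest reply is that section 2.9 should be read as a whole. The censoring rule stands beside the definition, and the exponential model, Kaplan-Meier curves and log-rank test all fit a time-to-event endpoint net of death. On that reading only the word percentage is loose. Net patency is a legitimate target and suits a hypothesis about how well a stent stays open. This stands in part: Kaplan-Meier is not wrong, and under independence it estimates net patency correctly. But the definition is worded as a share of patients, and with the mortality expected here a reader who takes it literally would be off by about 12 points in the ERCP arm.

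A second reply is that one minus the cumulative incidence has a weakness of its own. A patient who dies on day 10 counts as free of dysfunction, so higher mortality raises the apparent patency, and section 2.2 hopes that survival will differ between the arms. This stands. It is why the cumulative incidence should sit beside the Kaplan-Meier value and be read with mortality by arm, not replace it. Nor does it settle technical failures: censored on the day of treatment, they are outside both estimates.

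A third reply is that section 3.2 plans no between-arm difference in 180-day rates. This also stands. The 36.2 and 28.2 points show the size of the gap; neither is a planned result.

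**Conclusion.** The definition in 2.9 and the estimator in 2.9 and 3.2 do not match, and on the protocol's own mortality the mismatch is material. Dysfunction is 14.9% and 51.1% by Kaplan-Meier, against about 11.1% and 39.3% of patients. These figures rest on exponential, independent dysfunction and death, 10% monthly mortality and no other loss to follow-up.

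Three stronger readings are not supported:

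- **That the primary test or the sample size fails.** The log-rank test with deaths censored is a valid comparison of the cause-specific hazard of dysfunction, and the 29 events and 90 patients already allow for death.
- **That Kaplan-Meier is simply biased.** It estimates a different quantity, which needs its proper label.
- **That the planned confidence interval is too narrow.** The article says only that Greenwood's "formula will be used to estimate the confidence interval for the stent patency rate at 180 days after stent insertion". Greenwood's formula gives a variance and serves log(-log) limits equally well. The loss of coverage arises only if untransformed limits are used, and the 99% level is stated for other quantities. The choice may lie in an analysis plan that is not shown.

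**What to change.** 1. **Section 2.9:** label the 180-day Kaplan-Meier value as net patency with deaths censored, and stop describing it as a percentage of patients.
2. **Section 3.2:** keep the log-rank test and describe it as a comparison of cause-specific hazards. Add, per arm, the Aalen-Johansen cumulative incidence of dysfunction by day 180, with death as a competing event and a confidence interval.
3. **Reporting:** use the cumulative incidence for any statement about the share of patients who experience dysfunction. Show mortality by arm beside it, because early deaths count as free of dysfunction. State that technical failures censored at the treatment date are outside both estimates.
4. **Optional clarification, not a correction:** state the confidence level for the 180-day rate and form the Greenwood interval on the log(-log) scale.

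The cost is one more analysis and a few lines of wording. No new data are needed, since section 2.12 follows patients to death or the end of the study and section 2.10 lists overall survival as an endpoint. The downside is that the absolute rates will look less dramatic than the Kaplan-Meier values.
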